### Sample size

A total of *n* = 50 subjects (25 patients per treatment arm) will be included in the analyses.

### Randomization and blinding

The study will be performed in a randomized double-blind design. Neither participants, nor medical staff, investigators or outcomes assessors have insight into patients' allocation to each of the two study arms. Blinded study medication will be provided by the Hospital Pharmacy of the University Hospital. Subjects will be randomly assigned to the treatment arms of either verum or placebo at a 1:1 ratio. Prior to study initiation, a randomization list was generated by an external independent person using the nQuery software (Statistical Solutions Ltd., Cork, Ireland) and a block randomization design (block size *n* = 6). The assignment of medication to study participants is carried out by two persons, one acting as the operator and the second acting as the checker. Study drug intake will be supervised by the study staff.

### Data collection

A series of data during seven visits (V1 to V7) are collected during this trial.

#### Eating disorder-specific and general psychopathology

All subjects will be asked to fill in the Eating Disorder Examination-Questionnaire (EDE-Q) and the Eating Disorder Inventory-2 (EDI-2). The EDE-Q [99] evaluates eating disorder psychopathology in the past 28 days. It contains 22 items that have to be answered on a 7-point scale ranging from “never” to “every day”. It comprises four subscales assessing a) restraint, b) eating concern, c) weight concern and d) shape concern. Internal consistency of the German version was α = 0.97 in the validation study [100]. As this study includes inpatients whose meal intake is monitored by clinical psychologists and/or medical professionals, in order to ensure constant weight gain, the subscale “restraint” is not applicable in this study. The EDI-2 [101] is a self-report questionnaire with 91 items that assesses eating disorder psychopathology, but also inter- and intrapersonal aspects thought to be relevant for the development and perpetuation of eating disorders [101] (e.g. perfectionism, interpersonal distrust, lack of interoceptive awareness etc.). Higher scores indicate more severe psychopathology; only the total score will be considered in the analyses.

In addition, the State-Trait-Anxiety Inventory (STAI; [102]) for anxiety assessment, the Patient Health Questionnaire for the assessment of depression, (PHQ-9; [103]) and the Eating Disorder Quality of Life (EDQOL; [104]) for assessment of impairments in quality of life due to AN will be applied.

#### Blood sampling for general clinical assessment, neuroendocrinological parameters, sex hormones and appetite-regulating circuits

All subjects will undergo a dexamethasone-suppression test (DST), as an easy-to-perform test for the assessment of HPA axis activity at baseline and at the end of treatment at week 10 (EOT). In detail, 1 mg dexamethasone will be administered orally at 11.00 PM and cortisol in plasma will be assessed at 8.00 AM on the following day. Dexamethasone suppressors and non-suppressors will be considered in the statistical analyses.

In addition, an oral glucose tolerance test (OGTT) will be performed and plasma levels of ghrelin, leptin, insulin and glucose will be determined at baseline and at week 10 (EOT) to evaluate concentration changes in the course of this functional procedure.

Hormone levels of LH, FSH, estradiol, testosterone will be determined at baseline, week 2, week 6 and week 10 (EOT).

Blood samples will be obtained at baseline, at week 2 and week 10 to evaluate routine laboratory parameters (including blood count, fasting lipids, CRP, transaminases etc. for safety reasons). Interim assessments of further safety data (vital parameters, physical examination, urine pregnancy test etc.) are scheduled.

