**Methods:**

This is a randomized placebo-controlled clinical trial on the effects of a 10-week oral estrogen replacement (combination of ethinyl estradiol 0.03 mg and dienogest 2 mg) in adult female AN patients. The primary target is the assessment of the impact of sex hormone replacement upon neuropsychological performance by means of a neuropsychological test battery consisting of a test for verbal intelligence, the Trail making test A and B, a Go/No-go paradigm with food cues and the Wisconsin Card Sorting Test. Secondary targets include a) the examination of safety and tolerability (as mirrored by the number of adverse events), b) assessments of the impact upon eating disorder-specific psychopathology by means of the Eating Disorder Examination Questionnaire (EDE-Q) and the Eating Disorder Inventory-2 (EDI-2), c) the influence upon anxiety using the State-Trait-Anxiety Inventory (STAI), d) assessments of plasma cortisol levels during a dexamethasone-suppression test and appetite-regulating plasma peptides (ghrelin, leptin, insulin, glucose) during an oral glucose tolerance test and, e) a possible impact upon the prescription of antidepressants.

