## Methods

### Design

This prospective, randomized, double-blind, placebo-controlled, monocentre phase IIa clinical trial will compare outcomes for estrogen-progestin-treated and placebo-treated female AN patients upon a series of outcome parameters (see below) during inpatient AN-specific psychotherapy. Furthermore the study will investigate the safety and tolerability of the estrogen-progestin treatment compared to placebo. Patients in the verum group will receive a combination of ethinyl estradiol 0.03 mg and dienogest 2 mg over a period of ten weeks. The protocol is in accordance with the SPIRIT guidelines [98]. This clinical trial has been approved by the Federal Institute for Drugs and Medical Devices (Bundesinstitut für Arzneimittel und Medizinprodukte, BfArM, Bonn, Germany), the German Competent Authority for medicinal products and medical devices, and received the approval of the independent Ethics Committee of the Friedrich-Alexander-Universität Erlangen-Nürnberg, Germany. Monitoring of the study will be carried out by a qualified member of the Center for Clinical Studies, Erlangen, Germany according to the Good Clinical Practice (GCP) guidelines.

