### Recruitment

All participants are inpatients at the University Hospital Erlangen, Germany, Department of Psychosomatics and Psychotherapy. During an outpatient presentation before hospitalization, patients are screened by a medical professional with regard to inclusion and exclusion criteria and are asked to participate. Study inclusion takes place upon admission to our inpatient ward.

Female patients who gave consent to take part in the study and are already taking an OC will be asked to discontinue their contraceptive pill for a minimum of 28 days, in order to ensure a wash-out phase. Subjects will be asked to take additional contraceptive measures (at least two) to prevent pregnancy. Pregnancy tests in the course of the trial are scheduled; a pregnancy will immediately lead to discontinuation of study participation. All subjects will be examined by a staff member of the Department of Gynecology at the University Hospital Erlangen, as to ensure the absence of contraindications against the intake of an OC. A continuous intake of the study drug over a period of ten weeks is in accordance with common clinical OC practice, when due to medical reasons or patient’s preference menstruation should be omitted. Compliance to treatment will additionally be measured by interim measures of plasma sex hormones.

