Plasma sex hormones (4)		X		X	X	X		
OGTT for the assessment of plasma ghrelin, leptin, glucose and insulin (6)		X				X		
Routine laboratory tests (1)(2)(3) and urine dipstick		X		X		X		
Assessment of concurrent medication		X	X	X	X	X	X	X
Assessment of adverse events			X	X	X	X	X	X

1 hematology: hemoglobin (Hb), hematocrit, red blood cells, white blood cells, platelets, differential blood count, coagulation parameters (Quick/ PTT)

2 clinical chemistry: sodium, potassium, urea, chloride, creatinine, bilirubin, GOT, GPT, gamma-GT, alcaline phosphatase, lipase, LDH, CRP

3 fasting lipids

4 sex hormones: LH, FSH, estradiol, testosterone

5 dexamethasone-suppression test: 1 mg dexamethasone per os at 11.00 PM followed by fasting blood collection at 08.00 AM for plasma cortisol

6 OGTT (oral glucose tolerance test): blood draw before intake of glucose suspension (0 min) as well as 30, 60, 90 und 120 min after ingestion

*TMT A and B* Trail Making Test A and B, *WCST* Wisconsin Card Sorting Test

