### Outcome measures

The primary outcome measure is the change in neuropsychological performance based on the above described neuropsychological test battery after ten weeks of hormonal substitution with an estrogen-progestin-combination. The secondary outcome measures following the 10-week intervention are: a) incidence of treatment-emergent adverse events (AEs) (safety/tolerability) mirrored by the number of AEs (including AEs, adverse reactions [ARs], serious AEs, serious ARs and suspected unexpected serious ARs [SUSARs]), b) changes in psychopathology (EDE-Q, EDI-2, STAI, PHQ-9, EDQOL) mirrored by changes in sum scores, c) changes in cortisol mirrored by changes in plasma cortisol levels during a dexamethasone suppression test as well as changes in plasma concentrations of the appetite-regulating peptides ghrelin, leptin, insulin and glucose during an OGTT and d) changes in antidepressant medication mirrored by changes in their use.

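### The week-10 cortisol outcome cannot separate HPA change from an estrogen effect on cortisol binding, because only the verum arm is tested on oral ethinyl estradiol

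*Protocol article*

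**What the plan says.** **The test.** The blood sampling section describes a dexamethasone suppression test at baseline and at end of treatment: "1 mg dexamethasone will be administered orally at 11.00 PM and cortisol in plasma will be assessed at 8.00 AM on the following day". Footnote 5 to Table 1 repeats this: "1 mg dexamethasone per os at 11.00 PM followed by fasting blood collection at 08.00 AM for plasma cortisol". No cortisol value before dexamethasone is listed at either visit.

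**The outcome.** Secondary outcome c) in the Outcome measures section includes "changes in cortisol mirrored by changes in plasma cortisol levels during a dexamethasone suppression test". The blood sampling section adds: "Dexamethasone suppressors and non-suppressors will be considered in the statistical analyses". It gives neither a cut-off nor the role of that classification.

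**Exposure at the two tests.** The Design section states: "Patients in the verum group will receive a combination of ethinyl estradiol 0.03 mg and dienogest 2 mg over a period of ten weeks". The abstract gives the route as oral. Table 1 runs study-drug intake up to V6 (week 10), the visit with the second test. Patients already on an oral contraceptive are asked to "discontinue their contraceptive pill for a minimum of 28 days, in order to ensure a wash-out phase" (Recruitment section).

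**What is not listed.** The footnotes to Table 1 set out the laboratory measures in detail. CBG, free cortisol and salivary cortisol are not among them. The off-drug visit at week 16 has no suppression test. The Statistics section mentions no allowance for cortisol binding.

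**The concern.** Most cortisol in plasma is bound to CBG, and an ordinary plasma assay measures bound and free hormone together. Oral ethinyl estradiol increases CBG. Measured cortisol can therefore go up while free cortisol, the part that reflects HPA activity, stays the same.

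The design places this effect in one arm and at one time point. Both arms start without exogenous estrogen, and at week 10 only the verum arm is exposed. Any binding effect therefore enters the change score in the verum arm alone. Randomisation, blinding and baseline adjustment do not remove it, because the study drug causes it. A later analysis plan cannot recover free cortisol if neither free cortisol nor CBG was measured.

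HPA regulation is one of the aims stated in the Discussion. The trial could report poorer suppression on estrogen when only the binding protein changed, or could miss a true fall in free cortisol. The Statistics section says the data may feed later sample size calculations and new hypotheses, so the error could carry forward.

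**Working it through.** **1. The plan's own power figures.** The Statistics section uses 25 per arm and a two-sided t-test at 5%. The formula is power = P(|T| > 2.011), where T is noncentral t with 48 degrees of freedom and noncentrality d × √(25/2) = 3.536 × d.

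| Effect size d | Stated power | Recomputed |
|---|---|---|
| 0.60 | 55% | 54.7% |
| 0.70 | 68% | 67.9% |
| 0.80 | 80% | 79.2% |
| 0.86 | 85% | 84.6% |
| 0.94 | 90% | 90.3% |
| 1.04 | 95% | 95.0% |

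These reproduce to within one percentage point. No stated figure is wrong here; the point concerns what the cortisol value measures.

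**2. Exposure side by side.**

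| | Baseline test | Week-10 test |
|---|---|---|
| Verum | no exogenous estrogen | at the end of ten weeks of oral ethinyl estradiol |
| Placebo | no exogenous estrogen | no exogenous estrogen |

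Table 1 puts the first test in the treatment-start column (V3) and the text calls it baseline. I take it as preceding any drug effect.

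**3. Size of the artefact.** The documents give no figure for cortisol, its spread or CBG, so these inputs are assumptions:
- no true HPA change in either arm;
- binding multiplies verum total cortisol by r = 1.25, 1.5 or 2;
- log cortisol is normal with SD s between 0.5 and 1.0;
- 25 per arm, two-sided t-test at 5% (from the article).

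The spurious standardised difference is d = ln(r) / s. Its chance of reaching significance follows from the formula in step 1.

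| r | ln(r) | d at s = 0.5 | d at s = 1.0 | Chance at s = 0.5 | s = 0.6 | s = 0.8 | s = 1.0 |
|---|---|---|---|---|---|---|---|
| 1.00 | 0 | 0 | 0 | 5% | 5% | 5% | 5% |
| 1.25 | 0.223 | 0.45 | 0.22 | 34% | 25% | 16% | 12% |
| 1.50 | 0.405 | 0.81 | 0.41 | 80% | 65% | 42% | 29% |
| 2.00 | 0.693 | 1.39 | 0.69 | over 99% | 98% | 85% | 67% |

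Worked example: r = 1.5 and s = 0.5 give d = 0.405 / 0.5 = 0.81, about the 0.80 the trial is sized to detect. The noncentrality is 3.536 × 0.81 = 2.87 and the rejection rate is 80%.

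**4. Suppressor status.** Assume a true non-suppressor rate of 20% under any cut-off. The apparent verum rate is 1 − Φ(0.842 − ln(r)/s). For s from 1.0 down to 0.5 this gives 27-35% at r = 1.25, 33-49% at r = 1.5 and 44-71% at r = 2. These rates matter only if status at week 10 is used.

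**The case against.** **The mechanism and its size are not in the documents.** This is so. The direction is general pharmacology; the multiples, the proportional scaling and the log-SD are assumptions. The result is sensitive to the spread: at 1.5-fold the chance of a spurious finding falls from 80% at log-SD 0.5 to 29% at log-SD 1.0. This is why a range is given and no single rate is claimed.

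**The article does not say total cortisol, and a condensed article may leave the assay to the full protocol.** That is possible. But total cortisol is the ordinary meaning of plasma cortisol, nothing points to a free-cortisol assay, and the laboratory footnotes are detailed. If free cortisol is in fact assayed, the point falls away.

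**Stronger readings that the article does not support.**
- A reader might infer that the artefact runs against the trial's hypothesis. The three hypotheses concern neuropsychological performance, psychopathology and appetite-regulating circuits; none names cortisol.
- A reader might infer a planned comparison of suppressor rates between arms at week 10. The text says only that status will be considered, which could mean a baseline covariate.
- A reader might infer that the fasting sample of the glucose tolerance test (OGTT) supplies a pre-dexamethasone cortisol, and hence a percentage suppression. At baseline the OGTT is listed at V2 and the suppression test at V3. At week 10 both stand under V6 with no order given, so that sample may follow dexamethasone. Basal total cortisol on drug would also carry the same binding artefact.

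**It is one secondary outcome in a phase IIa trial.** This is correct and limits the weight of the point.

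**Conclusion.** The point stands in limited form. As described, the change in post-dexamethasone plasma cortisol at week 10 mixes HPA activity with a drug effect on cortisol binding that only the verum arm can have, and no listed measure separates them. The same holds for any suppressor classification made at week 10.

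The conclusion rests on plasma cortisol meaning total cortisol and on oral ethinyl estradiol raising CBG. Its size depends on the assumed multiple and spread, so the tabulated rates illustrate the problem and do not predict the trial's result. Even the mildest case shown, 12% at a 1.25-fold rise and log-SD 1.0, is more than twice the nominal 5%. The bias pushes measured verum cortisol upward, so an apparent worsening could be spurious and a real fall could be hidden.

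The neuropsychological primary outcome, the safety outcome and the psychopathology outcomes are not touched.

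**What to change.** **Preferred.** Assay CBG in the 8.00 AM post-dexamethasone samples already drawn at both tests, and define the HPA part of secondary outcome c) as the change in calculated free cortisol. The cost is about 50 patients × 2 tests = 100 extra assays and a changed outcome definition. No visit or blood draw is added and treatment is unchanged.

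**If that is not possible.** State that week-10 plasma cortisol and suppressor status on treatment are not evidence of an HPA effect, and use suppressor status only as measured at baseline. This costs wording and a weaker HPA claim.

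**Percentage suppression.** It should be added from the OGTT 0-min sample only if that sample is confirmed to precede the dexamethasone dose at week 10. Basal total cortisol on drug should not be read as free of the binding effect.

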### Neuropsychological performance

In addition, the neuropsychological performance of the subjects will be assessed using a neuropsychological battery consisting of the following tests: a) a test for evaluation of verbal intelligence and speech comprehension (“Wortschatztest”, WST; [105]), b) the Trail Making Test (TMT) [106] for the assessment of executive function, attention, information processing speed and planning ability, c) the WCST [107] as a test of frontal brain function. The test examines categorization ability among different categorization options and has an excellent sensitivity with regard to disturbed problem solving and perseverations, d) a go/no-go task as a paradigm for response inhibition, thus refraining an action initiation [108]. This task was programmed with Presentation® software (Version 16.0, Neurobehavioral Systems, Inc., Albany, CA, USA) to assess impairment of inhibitory control in response to food-related and control stimuli (for a detailed description see [109]). Changes on each test will be reported.

The neuropsychological assessment will be repeated after the 10-week intervention period.

A follow-up visit six weeks after EOT is scheduled. A summary of all study procedures is given in Table 1.

**Table 1 Tab1:** A synopsis of study procedures from visit 1 (V1) to visit 7 (V7)

	V1	V2	V3	V4	V5	V6		V7
	Screening	Baseline	Treatment start	Week 2	Week 6	Week 10 (EOT)		End visit (EOS) week 16
	month − 2 ± 2	day − 3 (±2)	day 1	day 15 (±3)	day 43 (±3)	day 73 (±3)		day 113 (±7)
Randomization			X					
Intake of study drug			X------>	-----------	------------	--------X		
Information about study objectives and informed written consent	X							
Inclusion and exclusion criteria	X	X						
Medical history		X						
Sociodemographic data		X						
Anthropometric data (height, weight, waist Circumference, hip circumference, BMI)		X					X	
Weight (BMI)		X	X	X	X		X	X
12-channel ECG		X					X	
Urine pregnancy test		X					X	
Vital parameters (HR, RR)		X	X	X	X		X	
Physical examination		X		X			X	
Gynecological examination		X						
Inclusion criteria and contraindications before first intake (gynecological findings, liver parameters, RR etc.)			X					
EDE-Q			X				X	X
EDI-2			X				X	X
STAI			X				X	X
PHQ-9			X				X	X
EDQOL			X				X	X
Neuropsychological test battery: verbal intelligence test, TMT A and B, Go/NoGo-test with food stimuli, WCST			X				X	
Dexamethasone-suppression test/plasma cortisol concentration (5)			X			X		
Plasma sex hormones (4)		X		X	X	X		
OGTT for the assessment of plasma ghrelin, leptin, glucose and insulin (6)		X				X		
Routine laboratory tests (1)(2)(3) and urine dipstick		X		X		X		
Assessment of concurrent medication		X	X	X	X	X	X	X
Assessment of adverse events			X	X	X	X	X	X

1 hematology: hemoglobin (Hb), hematocrit, red blood cells, white blood cells, platelets, differential blood count, coagulation parameters (Quick/ PTT)

2 clinical chemistry: sodium, potassium, urea, chloride, creatinine, bilirubin, GOT, GPT, gamma-GT, alcaline phosphatase, lipase, LDH, CRP

3 fasting lipids

4 sex hormones: LH, FSH, estradiol, testosterone

5 dexamethasone-suppression test: 1 mg dexamethasone per os at 11.00 PM followed by fasting blood collection at 08.00 AM for plasma cortisol

6 OGTT (oral glucose tolerance test): blood draw before intake of glucose suspension (0 min) as well as 30, 60, 90 und 120 min after ingestion

*TMT A and B* Trail Making Test A and B, *WCST* Wisconsin Card Sorting Test

### Statistics

The present trial is the first of its kind. Most trials have examined the effect of estrogen replacement upon bone mineral density in adolescent patients suffering from AN. Thus, in this phase IIa clinical trial, sample size cannot be calculated in the same way as in confirmatory phase III studies due to a missing valid base regarding effect sizes and variability of target parameters. However, a sample size calculation according to the results of a similar trial [97] with regard to the change in trait anxiety has been initially conducted. Following the treatment effects found in Misra et al. [97], *n* = 25 patients are needed in both groups in order to achieve a statistical power of at least 80% considering a two-sided t-test with the common significance level of 5%. With this number of patients, effect sizes (differences in means with a common SD = 1) of 0.80 can be detected (again with a two-sided t-test and significance level of 5%) with a power of 80%, e.g. at the end of treatment. Smaller effects sized of 0,60 or 0.70, could be only detected with a power of 55% or 68%. For a power of 85%, 90% and 95% effect sizes of 0.86, 0.94 or even 1.04 would be necessary.

Data of the present study may be used for future sample size calculations of confirmatory studies, as well as for the generation of new hypotheses. The intended statistical analysis follows the intention-to-treat principle. Differences between the treatment groups at baseline will be assessed using Fisher’s test for categorical variables and the non-parametric Mann-Whitney test for metric variables due to the relatively small sample size. For cross-sectional analysis of primary and secondary endpoints, adjustments for potential confounders and group differences at baseline by means of regression models will be applied. Missing outcome values will be imputed by corresponding baseline values. For longitudinal analyses, appropriate mixed models considering the longitudinal structure of data and interrelations due to random patient-specific effects will be used. Due to the robustness of this approach towards missing values, no imputation is planned for the longitudinal analyses. No interim analysis is scheduled. Effect sizes will be reported based on Cohen’s d for group differences for primary and secondary outcomes. Clinical improvements, amelioration in neuropsychological performance and restitution of hormonal aberrancies are all to be considered of clinical significance for patients with AN. The target parameters of safety and tolerability will be analysed descriptively (absolute and relative frequency with confidence intervals, mean values and medians with appropriate distributions).

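### The 80% power figure rests on a secondary outcome and on a t-test with complete data; it is not tied to the primary outcome or to its planned analysis, which replaces missing values by baseline

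*Protocol article*

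**What the plan says.** All places are in the Methods of the protocol article.

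- **Statistics, basis of the sample size.** A "sample size calculation according to the results of a similar trial [97] with regard to the change in trait anxiety has been initially conducted". From it the section concludes that 25 "patients are needed in both groups in order to achieve a statistical power of at least 80" per cent, using a two-sided 5% t-test.
- **Statistics, general power figures.** For the same 25 per arm: 80% power at 0.80 SD, 55% at 0.60 and 68% at 0.70; effects of 0.86, 0.94 and 1.04 for 85%, 90% and 95%. These are not attached to any endpoint.
- **Sample size.** Fifty subjects, 25 per arm, "will be included in the analyses". No dropout allowance is given.
- **Outcome measures.** "The primary outcome measure is the change in neuropsychological performance based on the above described neuropsychological test battery after ten weeks". The STAI, which measures trait anxiety, is among the secondary outcomes: "changes in psychopathology (EDE-Q, EDI-2, STAI, PHQ-9, EDQOL) mirrored by changes in sum scores".
- **Neuropsychological performance.** The battery has four tests (five if Trail Making A and B are counted separately), and "Changes on each test will be reported".
- **Statistics, analysis.** The analysis is by intention to treat. Cross-sectional analyses of primary and secondary endpoints use regression to adjust for confounders and baseline differences. "Missing outcome values will be imputed by corresponding baseline values". Mixed models without imputation are kept for the longitudinal analyses.

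**The concern.** The only quantitative support for 50 patients differs from the primary analysis in three ways: the outcome (trait anxiety, from a trial that the Background describes as in adolescents, while this trial enrols adults), the method (an unadjusted t-test rather than regression) and the data (25 observed outcomes per arm, with no missing values).

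The missing-data rule matters most. Setting a missing outcome to its baseline value gives that patient zero change, so any treatment difference is diluted in proportion to the share missing. The power figures take no account of this, although both statements stand in the same section.

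Two things are at stake. A null result on the battery could be taken as evidence against effects of 0.8 SD when the analysis had materially less power than 80% to find them. The plan also intends to report Cohen's d and to use the data for future sample-size calculations, and a diluted difference would carry over into those.

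**Working it through.** **1. The plan's own figures.** Inputs from Statistics: n = 25 per arm, SD = 1, two-sided α = 0.05. Exact two-sample t-test power uses the noncentral t with 48 degrees of freedom and noncentrality d·√(n/2). At d = 0.80 this is 0.80 × √12.5 = 2.83 against a critical value of 2.01, giving 79.1%.

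- d = 0.60 gives 54.7% and d = 0.70 gives 67.9% (stated: 55% and 68%).
- Effects needed for 85/90/95% are 0.865/0.936/1.041 (stated: 0.86/0.94/1.04).
- Exactly 80% needs 0.81 SD, or 26 per arm (80.7%).

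So the general figures reproduce to rounding. The trait-anxiety calculation cannot be checked, because its effect and SD are not given.

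**2. What imputation does to the effect.** Assumptions, none of them given in the document: a share m = 10, 20 or 30% missing at random and equally in both arms; a true effect of 0.80 in end-of-treatment SD units; baseline correlation ρ of 0.5 or 0.7; and an improvement common to both arms of 0 to 1 SD. A common improvement is plausible, since the Background says that cognitive deficits generally resolve with weight rehabilitation in inpatient care.

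The mean difference becomes (1 − m) × 0.80, that is 0.72, 0.64 or 0.56. The variance changes too:

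- *End-of-treatment values.* In an arm with mean change μ the variance is 1 + m(1 − m)μ². At m = 10% and no common improvement: 1 and 1 + 0.09 × 0.64 = 1.0576; mean 1.0288, root 1.014; effective d = 0.72/1.014 = 0.71; power about 69%.
- *Change scores.* At ρ = 0.5 the SD of change is √(2 − 2 × 0.5) = 1, and the variance in an arm is (1 − m) + m(1 − m)μ². At m = 10%: 0.9 and 0.9576; mean 0.9288, root 0.964; effective d = 0.72/0.964 = 0.747; power about 74%. The zero changes also shrink the SD, which softens the loss.

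**3. Baseline-adjusted regression, complete data.** The residual SD is √(1 − ρ²), or 0.866 at ρ = 0.5 and 0.714 at ρ = 0.7. The effective d is 0.80/0.866 = 0.92 and 0.80/0.714 = 1.12, giving about 89% and 97%.

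**4. Simulated power with baseline-value imputation, 25 per arm, α = 0.05.** The lower end of each range has 1 SD of common improvement, the upper end none. Repeat runs agree to within about two points.

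| Analysis | 0% missing | 10% | 20% | 30% |
|---|---|---|---|---|
| t-test, end-of-treatment values | 79% | 62–70% | 50–58% | 37–48% |
| t-test, change scores, ρ = 0.5 | 79% | 67–75% | 55–68% | 45–61% |
| Regression on baseline, ρ = 0.5 | 89% | 75–83% | 61–75% | 49–68% |
| Regression on baseline, ρ = 0.7 | 97% | 85–94% | 69–89% | 54–84% |

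**5. The same regression on observed outcomes only.** With 20% missing at random, power is about 80% at ρ = 0.5 and 92% at ρ = 0.7, whatever the common improvement.

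**6. Precision.** The unadjusted 95% CI half-width with complete data is 2.01 × √(2/25) = 0.57 SD.

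**7. Several primary tests.** A Bonferroni split over four or five tests would give 59% or 56% at 0.80 SD with complete data. The plan states no such correction, so these figures apply only if one is adopted.

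**The case against.** The strongest defence is that the protocol is open about its limits. It says that a phase IIa trial cannot be sized like a confirmatory one for want of a valid basis for effects and variability, names trait anxiety as the borrowed basis, and lists the STAI as secondary. Its general power figures fit any single test in the battery and already concede low power at 0.60 and 0.70 SD. The patients are inpatients with supervised drug intake, so dropout may be low. A condensed article may also leave dropout allowances to the full protocol.

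Much of this stands. A reader might infer any of the following, and the document supports none of them:

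- **That 80% power is claimed for the primary outcome and is untrue.** No such claim is made, and with no primary effect size, SD or dropout rate given, a failure to reach 80% cannot be shown.
- **That the arithmetic is wrong.** The gap between 79.1% and 80% is rounding.
- **That the power holds only if nobody drops out.** The t-test is used for sizing; the planned analysis is regression. If that includes the baseline score, power is still 80–83% at 10% missing with correlation 0.5, and above 80% at 20% missing with correlation 0.7, for common improvement up to 0.5 SD.
- **That multiple tests have already cut the power to 56%.** Without a correction the power per test is unchanged; what rises is the false-positive risk.

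What the defence does not answer is that the missing-data rule is stated in the article itself, applies to the primary endpoint, and changes the power that the same section reports. The caveat about phase IIa concerns unknown effect sizes, not this rule.

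**Conclusion.** The point holds in a limited form. The calculation is numerically sound, but it describes a secondary outcome and a complete-data t-test, and it is not linked to the neuropsychological primary outcome or to the stated analysis. For the t-test that was used for sizing, baseline-value imputation costs roughly 10 to 17 points at 10% missing and 20 to 30 points at 20%, taking end-of-treatment values at 0.80 SD. Planned regression recovers part of this: enough to stay at or above 80% in favourable settings and not in others. Which case applies depends on the missing share, the baseline correlation, the common improvement and whether the baseline score is always a covariate, and the document fixes none of these. The ranges are therefore conditional illustrations rather than estimates of this trial's power.

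**What to change.** Keep n = 50 and make four changes:

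1. Say that the trait-anxiety calculation concerns a secondary endpoint, and that the general figures (80% at 0.80 SD) are for one uncorrected test with complete data.
2. For the primary variable, state the detectable effect or the expected 95% CI half-width under the planned regression, for 0–30% missing. The unadjusted complete-data half-width of about 0.57 SD is the reference.
3. Analyse the primary outcome with adjustment for its baseline score and without baseline-value imputation.
4. If a multiplicity correction over the battery is adopted, give the power at the corrected level.

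The cost is in the text only; no extra patients are needed. The headline figure may look less favourable, and dropping the imputation means relying on a missing-at-random assumption, which should be stated and examined in a sensitivity analysis.
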